## Abstract

**Background:**

Hypertension is the leading global risk factor for mortality. Hypertension treatment and control rates are low worldwide, and delays in seeking care are associated with increased mortality. Thus, a critical component of hypertension management is to optimize linkage and retention to care.

**Methods/Design:**

This study investigates whether community health workers, equipped with a tailored behavioral communication strategy and smartphone technology, can increase linkage and retention of hypertensive individuals to a hypertension care program and significantly reduce blood pressure among them. The study will be conducted in the Kosirai and Turbo Divisions of western Kenya. An initial phase of qualitative inquiry will assess facilitators and barriers of linkage and retention to care using a modified Health Belief Model as a conceptual framework. Subsequently, we will conduct a cluster randomized controlled trial with three arms: 1) usual care (community health workers with the standard level of hypertension care training); 2) community health workers with an additional tailored behavioral communication strategy; and 3) community health workers with a tailored behavioral communication strategy who are also equipped with smartphone technology. The co-primary outcome measures are: 1) linkage to hypertension care, and 2) one-year change in systolic blood pressure among hypertensive individuals. Cost-effectiveness analysis will be conducted in terms of costs per unit decrease in blood pressure and costs per disability-adjusted life year gained.

**Discussion:**

This study will provide evidence regarding the effectiveness and cost-effectiveness of strategies to optimize linkage and retention to hypertension care that can be applicable to non-communicable disease management in low- and middle-income countries.

**Trial registration:**

This trial is registered with (NCT01844596) on 30 April 2013.

## Background

Cardiovascular disease (CVD) is the leading cause of mortality in the world, with 80% of CVD deaths occurring in low- and middle-income countries (LMICs) [1]. Hypertension, a major risk factor for ischemic heart disease, heart failure, and stroke [2], is the leading global risk for mortality [3]. The global cost of suboptimal blood pressure (BP) is estimated to reach nearly $1 trillion over the next decade [4]. Unless adequately controlled, hypertension will continue to be responsible for significant morbidity and mortality worldwide [5].

### Rationale for a focus on linkage and retention to care

Hypertension awareness, treatment, and control rates are low worldwide [6]. In Kenya, hypertension treatment and control rates have been reported at below 15% and 5%, respectively [7-9]. Given that hypertension may be asymptomatic, linkage and retention to care and medication adherence are particularly difficult challenges [10]. Delays in seeking hypertension care have been shown to be associated with increased mortality [11]. Thus, early linkage to hypertension care and successful retention to clinical services are critical components of hypertension management.

Studies of hypertension programs in sub-Saharan Africa have suggested that addressing financial barriers, provider-patient communication, and education may improve linkage, retention, and medication adherence [12-14]. Although preliminary qualitative research in western Kenya has revealed that community members understand that hypertension can cause significant morbidity and mortality [15], there are few known specific strategies to optimize linkage and retention to hypertension care in this setting.

### Components of the proposed intervention to optimize linkage and retention to care

Community health workers (CHWs) are members of a community who have received basic training to supply community members with access to health and social services, to educate individuals about various health issues, and to support overall community development [16]. CHWs have been utilized in communicable disease and maternal/child health programs [17]. However, they are only recently being deployed and evaluated in the context of non-communicable diseases [18], and the impact of CHWs on linkage and retention to hypertension care in Africa is relatively unknown.

Motivational interviewing and tailored communication-strategies intended to tailor interventions based on individual-specific behavioral assessments-have been shown to improve a variety of health behaviors [19,20]. In addition, mobile technology-based tools have the potential to improve the scope and efficiency of CHWs, and have demonstrated benefit for communicable diseases [21,22]. However, these strategies have not been rigorously evaluated in the context of hypertension management in LMICs. Thus, we plan to utilize a multidisciplinary implementation research approach [23] to develop and evaluate innovative community-based strategies, supported by mobile technology, to optimize linkage and retention to a hypertension management program in western Kenya.

### Aims

The central hypothesis of this study is that CHWs equipped with a tailored behavioral communication strategy, with or without smartphone technology, can increase linkage and retention of hypertensive individuals to a hypertension care program and thereby significantly reduce BP among these patients, when compared to usual care. We further hypothesize that these interventions will be cost-effective. Thus, the aims of this study are threefold. First, we aim to identify the facilitators and barriers to linking and retaining individuals with high BP to a hypertension care delivery program, using qualitative research methods. With this information, we will develop a communication strategy and a smartphone-based tool linked to an electronic health record. Second, we aim to evaluate the incremental effectiveness of the communication strategy and the smartphone-based tool in improving linkage and reducing BP among hypertensive patients. This will be done by conducting a three-arm cluster randomized controlled trial comparing: 1) usual care (CHWs with standard training on recruitment of individuals with any chronic condition); 2) CHWs with a communication strategy; and 3) CHWs with the communication strategy and equipped with smartphone technology. The co-primary outcome measures will be: 1) documented linkage to care, and 2) one year change in systolic BP (SBP) among those with hypertension. Third, we aim to evaluate the incremental cost-effectiveness of each intervention arm of the cluster randomized controlled trial, in terms of costs per unit decrease in BP and costs per disability-adjusted life year (DALY) gained.

## Methods/Design

### Setting

The United States Agency for International Development-Academic Model Providing Access to Healthcare Partnership (AMPATH) was initiated in Kenya in 2001 and has established a HIV care system in western Kenya that serves over 100,000 patients [24]. Based on that foundation, and in partnership with the Government of Kenya, AMPATH is expanding its clinical scope of work to include hypertension [25]. This study will be conducted within the AMPATH infrastructure in western Kenya, in the Kosirai and Turbo Divisions (Figure 1). Each Division is geographically and administratively divided into Community Units of approximately 5,000 individuals, with 9 units in Kosirai and 15 units in Turbo. Each Division has one rural health center staffed primarily by non-physician clinical officers trained to deliver a range of clinical health services [26], decentralized rural dispensaries staffed by nurses, and CHWs who are assigned to specific units. There has been a longstanding and positive relationship among AMPATH, the healthcare providers, and these communities [24,27,28]. The protocol has been approved by the institutional review boards of all participating institutions (Additional file 1), and the study is a registered on http://www.clinicaltrials.gov (identifier NCT01844596). Informed consent will be obtained from all study participants using a written informed consent form. During the consent process, participants will have the opportunity to request information and pose questions or concerns about their participation in the study.

**Figure 1 F1:**
[figure not shown]
AMPATH centers in Kenya numbered 1 to 35 and lettered A to Z; Kosirai and Turbo Divisions highlighted.

### Conceptual framework

Many behavior change models have been developed that focus on various types of health-related behavior and disease entities. In this study, we use the Health Belief Model, modified by incorporating the additional impact of emotional and environmental factors on behavior (Figure 2) [29]. The Health Belief Model is primarily a cognitive model based on the domains of perceived risk, perceived benefits, perceived barriers, cues to action, and self-efficacy [30]. While the Health Belief Model has been successfully applied to hypertension-related research in a variety of settings and populations [31,32], we have expanded the model to incorporate the complex interactions among cognition, emotion, environment, and behavior. Emotional factors include desires, aspirations, fears, and worries that may directly motivate action or serve as a powerful lens to weigh advantages and disadvantages of alternative actions [33]. Environmental factors include socioeconomic factors, costs, political constraints, and cultural norms, which may facilitate or constrain an individual’s behavior.

**Figure 2 F2:**
[figure not shown]
Modified Health Belief Model: personal (cognitive and emotional) and environmental factors.

### Facilitators and barriers to linkage and retention to hypertension care

We will use a combination of qualitative research methods, including traditional community assemblies (*mabaraza*) and focus group discussions (FGDs), to identify the facilitators and barriers to linkage and retention to hypertension care. In East Africa, the *mabaraza* are used to address a wide variety of situations, ranging from local disputes to exchange of information. This unique and novel qualitative research setting has been used as a form of participatory action research related to HIV care [34]. The *mabaraza* allow us to organize large and heterogeneous groups of individuals, which complement the purposive sampling inherent in FGDs.

For all qualitative sessions, we have developed moderator guides, which have been used by trained moderators fluent in the local languages. We have thus far conducted 6 *mabaraza* and 17 FGDs using purposive sampling by age, sex, occupation, and distance from nearest health facility. Participatory techniques have been used to elicit emotional elements and promote group interactions [35]. All sessions have been audio-recorded, transcribed, and translated into English. Content analysis of the transcripts will be performed using both deductive (*a priori*) and inductive (emerging) codes [36]. The coded items will be grouped together into distinct themes, and relationships among these themes will be formulated.

Using the data gathered in the formative qualitative sessions, we will use a participatory, iterative design process to develop a tailored behavioral communication strategy for CHWs to use as they interact with patients and their families [37]. CHWs will be trained to engage in practical, motivating, proactive problem-solving with patients around such issues as transportation, clinic scheduling, home responsibilities, stigma concerns, and other issues that may be uncovered by the qualitative research. We will develop both a hard copy version and a smartphone version to be used by CHWs.

The smartphone version will be linked to the electronic health record and will have two functionalities: 1) ability to provide each CHW with an automatically updated list of individuals requiring follow up; and 2) the ability to provide real-time decision support based on the communication strategy, using data collected by the CHW during a patient encounter. The decision support will use branching logic and decision trees based on specific motivational messages, as well as simple clinical care algorithms appropriate for CHWs. The smartphone technology will allow for alternative messaging modalities, such as images and recordings (both audio and visual).

### Cluster randomized controlled trial

We will conduct a cluster randomized controlled trial with three intervention arms: 1) usual care - CHWs with standard training on recruitment of individuals with any chronic condition (‘UC’); 2) CHWs with a tailored behavioral communication strategy (‘TBCS’); and 3) CHWs with a communication strategy who are also equipped with smartphone technology (‘TBCS-ST’). The unit of randomization will be the community unit, since randomization by CHW or patient would be at risk for contamination, as all CHWs and nearly all patients within one community unit are affiliated with the same dispensary. Randomization will be stratified by division, so that the 9 units of Kosirai will be randomized separately from the 15 units of Turbo. The units will be randomly allocated to one of the three intervention arms. The randomization process will be conducted centrally by biostatisticians at Brown University (Providence, United States). We will compare key variables (such as age, sex, severity of initial SBP, different treatment regimens, previous history of hypertension treatment, socioeconomic status, body mass index, physical activity, alcohol consumption, and tobacco use) to ensure balance among the randomized groups, and make adjustments in our treatment effect estimates as needed using logistic regression adjustment.

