**Figure 3 F3:**
[figure not shown]
**Classification of participants in trial.** BP = Blood Pressure; CHW-S = usual care arm; CHW-B = tailored behavioral communication strategy arm; CHW-BT = communication strategy and smartphone technology arm; CU- Community Unit.

An individual who does not present to the dispensary within one month will be defined as ‘non-linked’ and will be identified by the dispensary nurse. At that point in time, a CHW will be assigned to visit that individual to encourage linkage to care. Those who do not link to care within one month of the second CHW visit will be considered ‘chronic non-linked’. Individuals who ultimately link to care will be characterized as ‘self-linked’ (linked on their own without CHW intervention) or ‘CHW-mediated linked’. At the dispensary, each individual who has linked will have a repeat BP measured, and those with repeat elevated BP will be entered into the hypertension management program as patients. Patients will be managed according to the AMPATH hypertension protocol that is derived from consensus guidelines for hypertension management, using drugs contained in the Kenyan national formulary [38-40]. Patients who miss a clinic appointment for more than one month will be considered ‘non-retained’. Patients who are retained in care will be defined as either ‘self-retained’ (retained on their own without CHW intervention) or ‘CHW-mediated retained’. An individual will be considered ‘lost to follow up’ if they does not return to the clinic for three months despite CHW visits. The 12-month follow up BP will be measured in the dispensary, in order to mimic real-world practice.

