### Outcomes

The co-primary outcome measures will be: 1) documented linkage to care, defined as a confirmed dispensary visit within one month of either home-based testing (self-linked) or a CHW visit (CHW-mediated linked), and 2) one-year change in SBP among those with hypertension. Our ultimate goal is to implement an intention-to-treat comparison of change in SBP among confirmed hypertensive individuals. However, confirmation of hypertensive status requires at least two BP measurements, and this requires successful linkage to care (Figure 3). Hence, we have opted for the co-primary outcome approach. We will compare the proportion linked to care between the three study arms using conditional logistic regression. For the SBP outcome, we will implement an intention-to-treat comparison of change in SBP between the three study arms. For those who are not successfully linked to care, we will use imputed SBP values. Full details of our approach to imputation appear in Additional file 2.

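### Covariate adjustment depends on an observed balance check, may include treatment given after linkage, and names only a method that cannot adjust the SBP outcome

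*Protocol article*

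**What the plan says.** Under Cluster randomized controlled trial, the protocol article plans to compare key variables across arms "to ensure balance among the randomized groups", and then to "make adjustments in our treatment effect estimates as needed using logistic regression adjustment". The list is introduced as examples, so it is open. It names ten variables, among them "severity of initial SBP, different treatment regimens, previous history of hypertension treatment".

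Under Study participants (the text after Figure 3), individuals who link have BP measured again at the dispensary, and "those with repeat elevated BP will be entered into the hypertension management program as patients". The central hypothesis under Aims is that the strategies "can increase linkage and retention of hypertensive individuals to a hypertension care program and thereby significantly reduce BP among these patients".

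Under Outcomes, the two co-primary measures are handled separately. For linkage: "We will compare the proportion linked to care between the three study arms using conditional logistic regression". The second measure is "one-year change in SBP among those with hypertension", and the plan is: "For the SBP outcome, we will implement an intention-to-treat comparison of change in SBP between the three study arms". SBP is imputed for those who do not link; the details are in Additional file 2, which is not shown.

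**The concern.** One sentence fixes how the treatment effect estimates may be adjusted, and it has three weaknesses.

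- **Selection after seeing the data.** Whether to adjust, and for what, depends on observed imbalance, with no criterion and an open list. The analysis behind both co-primary estimates is then not fixed in advance, which sits badly with the Bonferroni control of overall type I error described under Statistical power.
- **A possible mediator among the covariates.** Treatment regimen has no date. If it means treatment under the hypertension program, it follows randomisation and is part of how the intervention is meant to lower SBP. Adjusting for it would remove some or all of the effect the trial seeks to show.
- **A method that fits one outcome of two.** Logistic regression is the only adjustment method named for the treatment effect estimates, and one of the two co-primary outcomes is continuous.

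**Working it through.** **Inputs from the protocol article.** Community unit population 5,000; 45.3% above age 20; one-third screened per year; about 30% with elevated SBP; expected linkage 40% (UC), 60% (TBCS) and 80% (TBCS-ST); 9 + 15 = 24 community units, so 8 per arm if split equally.

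**Assumed, not in the document.** SBP effect of being treated 10 mmHg (range 5 to 15); SD of change 15 mmHg; SBP ICC 0.02; everyone who links is treated.

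**1. The plan's own figure.** 5,000 × 0.453 × 1/3 × 0.30 = 226.5, which agrees with the stated 226 referred per unit per year. No figure in the article is disputed here.

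**2. Timing of treatment regimen.** Three statements, side by side:

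- The covariate list has regimens and previous treatment history as separate items, so the first is probably not past treatment.
- Entry to the program requires linkage and a repeat elevated BP, so program treatment comes after randomisation and after linkage.
- The hypothesis runs from intervention to linkage and retention, and *thereby* to lower BP, so program treatment lies on the causal path.

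**3. What the balance check would see.** At the expected linkage rates, at least 100 − 40 = 60%, 100 − 60 = 40% and 100 − 80 = 20% of participants would have no program regimen in UC, TBCS and TBCS-ST. On the post-linkage reading, regimen is unbalanced if the intervention works, and that imbalance is what triggers adjustment. For the linkage outcome the variable would also partly encode the outcome, since having a program regimen implies having linked.

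**4. Size for SBP.** If the effect runs wholly through linkage and treatment, arm difference = (difference in linkage) × (effect of being treated):

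| Contrast | Difference in linkage | 5 mmHg | 10 mmHg | 15 mmHg |
|---|---|---|---|---|
| UC vs TBCS | 0.20 | 1 | 2 | 3 |
| TBCS vs TBCS-ST | 0.20 | 1 | 2 | 3 |
| UC vs TBCS-ST | 0.40 | 2 | 4 | 6 |

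A simulation at 10 mmHg (8 units per arm, 226 per unit, 300 replicates, linear model) gave unadjusted effects of about −1.9, −2.0 and −4.0 mmHg in the same row order. After adjustment for the treatment variable each was within about 0.1 mmHg of zero. The effect vanishes because full mediation was assumed. If a share f passes through the adjusted variable, about (1 − f) of it remains: with f = 0.5, 2 mmHg becomes 0.5 × 2 = 1 mmHg.

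**5. Freedom left by the rule.** Ten named variables, each in or out, allow 2^10 = 1,024 adjustment sets before any unlisted variable is considered. With about 8 units per arm and three pairwise comparisons, some chance imbalance is to be expected. The effect on type I error cannot be computed, because no selection criterion is stated.

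**6. Method against outcome.** Linkage is binary and has a logistic model under Outcomes, so logistic adjustment fits it. Change in SBP is continuous, and logistic regression cannot estimate an adjusted difference in it.

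**The case against.** **Logistic regression may refer to linkage only.** A reader might infer that change in SBP will itself be fitted by logistic regression. The document does not support that. Outcomes ties conditional logistic regression to linkage and describes the SBP comparison separately, without naming a model. The adjustment sentence can be read as concerning linkage, the outcome on which the study is powered. An unnamed SBP model in an article is no fault, as the analysis plan may give it. What stands is narrower: the sentence speaks of the treatment effect estimates in general and names a method that can serve only one of the two.

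**Regimen may mean treatment at baseline.** The other listed variables are participant characteristics, the declared purpose is balance between randomised groups, and a post-linkage regimen does not exist for people who never link. Current treatment at home-based testing, as distinct from past treatment, is a coherent reading. The text does not settle it, so adjustment for a mediator is a risk, not an established feature of the plan.

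**Precision from baseline SBP.** It is tempting to add that adjusting for baseline SBP only when it is unbalanced wastes 20 to 30% of variance. At individual level the ratio of ANCOVA to change-score variance is (1 + r)/2, or 0.70, 0.75 and 0.80 for an assumed r of 0.4, 0.5 and 0.6. That saving cannot be claimed here. It assumes equal variances at both times, which is doubtful when entry requires elevated BP, and it ignores clustering. The within-unit share of a unit mean's variance is ((1 − ICC)/226)/(ICC + (1 − ICC)/226): 0.00434/0.02434 = 18% at ICC 0.02 and 0.00420/0.05420 = 8% at ICC 0.05. A 25% within-unit saving then lowers total variance by about 0.25 × 18% = 4.5% or 0.25 × 8% = 2%, unless baseline SBP also explains differences between units, which is unknown. Nor does the article say that change will be analysed without baseline SBP, which is on its list.

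**An analysis plan could settle all this.** It could, but the article states a rule rather than leaving one open, and as stated the rule is unsound.

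**Conclusion.** The point holds in limited form. As written, covariates for the treatment effect estimates depend on observed imbalance, with no criterion and an open list. The list contains an undated treatment variable that is probably, but not certainly, post-randomisation. The only adjustment method named cannot serve the SBP co-primary outcome.

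The potential loss is part or all of the SBP effect: 2 mmHg per 20 points of linkage under the assumed 10 mmHg treatment effect and full mediation, and 1 to 3 mmHg over an assumed 5 to 15 mmHg. This illustration treats everyone who links as treated and SBP as observed for all, whereas treatment needs a repeat elevated BP and non-linked participants have imputed SBP. If regimen was meant at baseline, this loss does not arise, and the data-dependent selection and the mismatch of method remain. No figure is offered for error-rate inflation or for precision gained. Confidence is medium, because the key item has no date. The change is worth making under either reading.

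**What to change.** Replace the balance-and-adjust sentence with wording to this effect:

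> Baseline variables will be described by arm. Whatever the observed balance, both co-primary analyses will adjust for division (the randomisation stratum) and for a short prespecified set of variables recorded at or before home-based testing, including baseline SBP. Linkage will be adjusted within the logistic model given under Outcomes. Change in SBP will be analysed with a linear model that includes baseline SBP as a covariate and accounts for community unit. Treatment started after linkage will not be adjusted for in either analysis.

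In the list, either delete the treatment regimens item or restrict it to treatment in use at home-based testing. Keep the set short, since there are only 24 units, and name its members before outcome data are seen. If the conditional model for linkage already conditions on division, say so, and that part is met. The linkage model and the change-in-SBP outcome under Outcomes stay as they are.

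The cost is protocol or analysis plan wording. Baseline SBP and division are recorded by design, the other candidates are already on the article's list, and Trial status says the randomised part has not begun.
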